#### Secondary outcomes

Effectiveness:

Length of hospital stay, measured in hours from admission to discharge.Time spent on oxygen therapy, measured in hours.

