Given the variation in guidelines and clinical practice, the lack of high-quality evidence and the significant potential benefits for patients and their parents, studies on effective and safe SpO2 thresholds for children with respiratory distress are urgently needed. This study aims to investigate whether an SpO2 threshold of 88%, compared with 92%, in children aged 6 weeks to 12 years admitted with respiratory distress, results in a safe reduction in length of hospital stay and is cost-effective from a societal perspective.

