### Outcomes

#### Primary outcome

The primary outcome of this trial is the time from admission to when all prespecified discharge criteria are met. Prespecified discharge criteria are:

No need for supplemental oxygen for 4 hours, including a period of sleep for children aged <2 years.Clinically fit for discharge with normal or minimally increased respiratory rate AND no or mild respiratory distress, as judged by nurses and physicians using the Parshuram *et al*^15^ scoring system, commonly used in Dutch paediatric practice as part of the Paediatric Early Warning Scale.^16^No need for in-hospital feeding or medication by nasogastric tube.No need for in-hospital intravenous treatment.No need for in-hospital nebulised bronchodilator treatment.No need for in-hospital treatment with metered dose inhalator inhalations more often than every 3 hours.No need for high flow delivered by high flow nasal cannula or nasal prongs.

Nursing staff continuously monitor discharge criteria and register them when met. Clinical fitness for discharge is checked every 4 hours, starting 4 hours after oxygen therapy is first stopped. If oxygen therapy is not initiated, this criterion is checked every 4 hours starting 4 hours after randomisation. In clinical practice, the actual discharge time may be later than when all discharge criteria are met. The reasons for any delay in discharge will be documented.

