#### Safety outcomes

Number of PICU admissions.Number of unscheduled readmissions and revisits to healthcare providers, as reported by parents in follow-up questionnaires and registered from patient electronic health records.Duration of symptoms, defined as time in days from admission to meeting the following criteria:Resolution of cough (less than one cough every hour), as reported by parents.Resolution of dyspnoea, as reported by parents.Cessation of scheduled salbutamol use, as reported by parents.Time in days from admission to return to normal health, as reported by parents.Time in days from admission to return to school/day care, as reported by parents.Patient quality of life during follow-up, measured by digital questionnaires at discharge, 7 days, 28 days and 90 days after discharge by EuroQol Five Dimensions Health Questionnaire Youth (EQ-5D-Y) (by patient or by parent proxy form). For ages 6 weeks to 2 years, only the EuroQol Visual Analogue Scale (EQ-VAS) is used, as this is the only tool with good clinimetric properties in this age group which can be compared with the full 6 weeks to 12 years age range.^17^ For ages 2 and 3 years, a version of the EQ-5D-Y with modified wording is used, developed in an Australian study (currently in submission) and has been translated with the help of the EuroQol offices. For ages 4–12 years, the EQ-5D-Y is used (proxy version for up to 8 years, self-complete version for 8–12 years), validated in this age group.^18 19^Parental anxiety up to 1 month after discharge, measured by digital questionnaires at discharge, 7 days and 28 days after discharge by the anxiety items on Hospital Anxiety and Depression Scale.^20^Overall paediatric health was measured by digital questionnaires of International Consortium for Health Outcome Measurement (ICHOM) Patient-Reported Outcomes Measurment Information System (PROMIS) set at discharge, 7, 28 and 90 days follow-ups.

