#### Economic evaluation

The economic evaluation aims to relate the incremental costs of an SpO2 threshold of 88% (intervention) with an SpO2 threshold of 92% (control) to the incremental health effects. Both cost-effectiveness analysis and a cost–utility analysis will be performed from a societal and healthcare perspective according to Dutch guidelines with a time horizon of 90 days postdischarge.^21^ Discounting is not necessary as the time horizon is less than 12 months. Costs will be measured from a societal perspective using web-based questionnaires based on the iMTA Medical Consumption Questionnaire and iMTA Productivity Cost Questionnaire at discharge and 90 days after discharge.

Cost categories include:

Healthcare costs (primary/secondary/tertiary care, complementary care and home care).Lost productivity costs of the parents (absenteeism from paid and unpaid work).Patient costs (informal care and other care services paid for by the patients themselves).

Valuation follows Dutch cost guidelines,^22^ with absenteeism from paid work using the friction cost approach. Effect measures in the economic evaluation will include:

Length of hospital stay.Overall paediatric health by ICHOM PROMIS set.Parent anxiety.Quality-adjusted life-years (EQ-5D-Y with Dutch reference values).^23^

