##### Secondary study parameter(s)

All analyses of secondary study parameters will use an intention-to-treat approach, with a per-protocol approach performed as a sensitivity analysis. All point estimates will be presented according to the distribution of the data (mean/median with standard deviation (SD) / Interquartile Range (IQR)).

Count outcomes: For count outcomes like PICU transfers, readmission and unscheduled visits to healthcare providers, multilevel Poisson regression will be used.Oxygen therapy duration: To investigate differences in time on oxygen therapy between groups, multivariable linear regression will be applied.Time-to-event outcomes: For outcomes such as time to last day of cough and/or salbutamol use, time to normal activities and time to discharge, Cox proportional hazards models will estimate the treatment effect. Time-to-event data will be either interval-censored or right-censored. All models will be adjusted for hospital, age, gender, respiratory distress severity at baseline, diagnosis and smoking by parents/patients if possible.Quality of life, anxiety measures and ICHOM PROMIS scores are continuous repeated measures and will be analysed using multilevel models, with random effects accounting for multiple measurements within each individual.Exploratory subgroup analyses: These will be based on diagnosis, age and skin type, as skin type might influence the accuracy SpO2 measurement.^24^,^26^ Skin type will be recorded in the discharge questionnaire by the parent as one of the six skin types defined by Fitzpatrick.^27^

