### Procedures for recording and reporting adverse events

In this low intervention trial, procedures for recording and reporting of (severe) adverse events ((S)AEs) are based on a risk-proportionate approach. They follow recommendations from the Dutch Central Committee on Research Involving Human Subjects (CCMO).

Recording AEs: All AEs reported spontaneously by the subject, his/her parent(s)/guardian(s) or observed by the investigator or his staff will be recorded up until 28 days of follow-up or until the end of the disease, whichever comes last, but no longer than full study follow-up.

Exceptions include:

Elective hospital admissions or procedures.Common symptoms of bronchiolitis, viral wheeze or lower respiratory tract infections, such as coughing, dyspnoea, rhinitis, fatigue, sleep disturbance, food intolerance and bronchodilator requirement. A selection of these events (duration of cough, duration of dyspnoea and bronchodilator use) are recorded and reported within the patient questionnaires as safety parameters.Deterioration in respiratory symptoms during admission, identified by the need for high-flow nasal cannula or CPAP, is recorded and reported within the electronic Case Report Form (e-CRF).Hospital readmissions (SAE) or reassessments (AE) are recorded and reported within the e-CRF.

Immediate reporting (within 24 hours): The following SAEs are critical to safety evaluations and require immediate reporting from the investigator to the sponsor:

PICU admissions.SAEs that result in persistent disability/incapacity or death.Other SAEs likely related to the study intervention, such as readmissions within 28 days.

Non-reporting SAEs: No reporting is required for the following (S)AEs as no causal relationship with the study procedure is expected:

AEs and SAEs occur after signing informed consent but before patient randomisation or initiation of the assigned SpO2 threshold.SAEs not part of the listed SAEs requiring reporting and not considered Suspected Unexpected Serious Adverse Reaction (SUSAR).

Follow-up on AEs: All AEs will be followed until they have been resolved or until a stable situation has been reached. Follow-up may require additional tests or medical procedures as needed and/or referral to a general physician or a medical specialist.

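### Length of stay ends at discharge, but the economic evaluation sets it against costs that run to 90 days, so hours returned through readmission are not subtracted from hours saved

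*Protocol article*

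**What the plan says.** The aim, at the end of the Introduction, is to find out whether the 88% threshold "results in a safe reduction in length of hospital stay and is cost-effective from a societal perspective". Two outcomes bear on hospital time:

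- Primary outcome: "The primary outcome of this trial is the time from admission to when all prespecified discharge criteria are met".
- Secondary outcomes, effectiveness: "Length of hospital stay, measured in hours from admission to discharge".

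Readmissions appear elsewhere, always as events:

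- Safety outcomes: "Number of unscheduled readmissions and revisits to healthcare providers, as reported by parents in follow-up questionnaires and registered from patient electronic health records".
- Secondary study parameter(s): "For count outcomes like PICU transfers, readmission and unscheduled visits to healthcare providers, multilevel Poisson regression will be used".
- Adverse event procedures: "Hospital readmissions (SAE) or reassessments (AE) are recorded and reported within the e-CRF". Readmissions within 28 days are also listed there for immediate reporting.

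The Economic evaluation section plans its analyses "with a time horizon of 90 days postdischarge" and counts primary, secondary and tertiary care among the costs. Under "Effect measures in the economic evaluation will include" it lists four items, and length of hospital stay is the first. It gives no separate definition or time window for that item. The statistical section for the economic evaluation then forms each ratio as the difference in mean costs over the difference in mean effects.

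**The concern.** A lower threshold is expected to shorten stay by letting children meet the discharge criteria sooner. One possible offset is return to hospital. A stay outcome that stops at discharge cannot tell hours saved from hours moved to a second admission. For example, a child discharged at 60 h and later readmitted for 72 h contributes 60 h, against 72 h for a child discharged at 72 h who never returns. In total hospital time the first child has used 132 h.

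The economic ratio is where this matters most. A readmission within 90 days is hospital care, so its cost enters the numerator. If length of stay keeps its only stated definition, the hours of that readmission do not enter the denominator. The two sides then cover different periods, and the cost per hospital hour saved does not describe net hours.

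**Working it through.** **The plan's own figure.** Inputs from Sample size and feasibility: difference 12 h, SD 48 h, alpha 0.05, power 80%. With a two-sided test, n per arm = 2 × (1.960 + 0.842)² × 48² / 12² = 251.2, which rounds up to 252; 251 per arm gives power 0.7997. Allowing for 10% dropout, 502 / 0.90 gives 558 and 504 / 0.90 gives 560. The stated 251 per arm and 560 in total reproduce. They are for time to meeting the discharge criteria, so this point does not touch them.

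**What each side of the ratio covers.**

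| Side | Period | Readmission within 90 days |
|---|---|---|
| Costs | to 90 days after discharge | included, as secondary or tertiary care |
| Length of stay, as defined under Secondary outcomes | admission to discharge | hours not included |

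No section adds readmission hours to any measure of stay.

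**Size.** The article gives neither a readmission rate nor the length of a readmission, so both are assumptions. Take an index saving equal to the 12 h target, an excess proportion d readmitted in the 88% arm, and L hours per readmission. The upper value L = 72 h borrows the planning mean stay.

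- Hours returned per randomised child = d × L
- Net saving = 12 − d × L
- Factor by which the denominator is overstated = 12 / (12 − d × L)

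| Excess d | L | Returned | Share of 12 h | Net | Factor |
|---|---|---|---|---|---|
| 1 point | 24 h | 0.24 h | 2% | 11.76 h | 1.02 |
| 2 points | 48 h | 0.96 h | 8% | 11.04 h | 1.09 |
| 3 points | 72 h | 2.16 h | 18% | 9.84 h | 1.22 |
| 5 points | 48 h | 2.4 h | 20% | 9.6 h | 1.25 |
| 5 points | 72 h | 3.6 h | 30% | 8.4 h | 1.43 |
| 10 points | 72 h | 7.2 h | 60% | 4.8 h | 2.50 |

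With equal readmission hours in the two arms, nothing is returned and the factor is 1. The full 12 h would be offset only at an excess of 12/72 = 16.7 points, 12/48 = 25 points or 12/24 = 50 points.

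**Would the readmission count show it?** Assume 5% readmitted and 280 per arm (560 / 2). The 95% half-width for a difference with 5% in both arms is 1.96 × √(2 × 0.05 × 0.95 / 280) = 3.6 points. By a simple normal approximation, power is about 30% for 5% against 8% and about 62% for 5% against 10%. For 5% against 15% the standard error is about 2.5 points and z is about 4, so that excess would be seen. Small and moderate excesses could go undetected; the largest one in the table would not.

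**The case against.** Admission-to-discharge stay is a clear and measurable definition, and total hospital hours answer a different question. The aim is a safe reduction, and readmissions are weighed as a safety outcome, taken from parents and records and tested with a multilevel model. Keeping effectiveness and safety apart also has merit, because merging them can hide an excess of readmissions inside a net gain in hours. This stands, and it is why the secondary outcome should not be replaced.

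It can also be said that the economic section does not itself restrict length of stay to the first admission, and that a health-economic plan might define it more widely. That is fair: the restriction is carried over from the Secondary outcomes section. But it is the only definition the article gives, and nothing in the article contradicts it.

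A reader might go further and infer that the trial's effectiveness result is inflated, that readmissions are ignored, or that most of the benefit could be illusory. The document supports none of these. The powered result rests on time to discharge criteria. Readmissions are tested as events and their costs already count against the intervention. The 60% figure needs an assumed 10-point excess at 72 h each. Nor can an excess be taken for granted, since children in both arms must meet the full set of discharge criteria.

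**Conclusion.** The point holds in a limited form. Followed as written, the cost per hospital hour saved sets costs to 90 days against hours that end at discharge. The secondary stay outcome likewise does not subtract hours spent in hospital on readmission. The readmission count does not make up for this, because it measures events rather than hours.

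The misstatement arises only if readmission hours differ between arms. Its size cannot be fixed from the document: under the assumed excesses of 1 to 10 points at 24 to 72 h it runs from 0.24 to 7.2 h of the 12 h target, and it is zero if the arms are equal. If the 88% arm had fewer readmission hours, the index stay would understate the saving. The primary outcome, the sample size and the cost-utility analysis stand as they are. The point concerns a secondary outcome and one of four economic effect measures, and is worth considering as a cheap improvement rather than a necessary correction.

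**What to change.** 1. Keep admission-to-discharge stay as the secondary effectiveness outcome.
2. Add total hospital hours, meaning the index stay plus all unscheduled readmissions, as a supporting effectiveness analysis.
3. In the economic evaluation, define the length-of-stay effect as total hospital hours from first admission through 90 days after discharge, so that it covers the same period as the costs. A 28-day window would leave the mismatch in place.

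The cost is modest but not nil. A reader might suppose that the data are already in hand, but the article states that readmissions are recorded, not that their admission and discharge times are. Table 1 schedules readmissions at +28 days only. Those times would have to be extracted through day 90 from the electronic health records already consulted for readmissions. Total hours will also be somewhat more variable than the index stay.

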#### Safety outcomes

Number of PICU admissions.Number of unscheduled readmissions and revisits to healthcare providers, as reported by parents in follow-up questionnaires and registered from patient electronic health records.Duration of symptoms, defined as time in days from admission to meeting the following criteria:Resolution of cough (less than one cough every hour), as reported by parents.Resolution of dyspnoea, as reported by parents.Cessation of scheduled salbutamol use, as reported by parents.Time in days from admission to return to normal health, as reported by parents.Time in days from admission to return to school/day care, as reported by parents.Patient quality of life during follow-up, measured by digital questionnaires at discharge, 7 days, 28 days and 90 days after discharge by EuroQol Five Dimensions Health Questionnaire Youth (EQ-5D-Y) (by patient or by parent proxy form). For ages 6 weeks to 2 years, only the EuroQol Visual Analogue Scale (EQ-VAS) is used, as this is the only tool with good clinimetric properties in this age group which can be compared with the full 6 weeks to 12 years age range.^17^ For ages 2 and 3 years, a version of the EQ-5D-Y with modified wording is used, developed in an Australian study (currently in submission) and has been translated with the help of the EuroQol offices. For ages 4–12 years, the EQ-5D-Y is used (proxy version for up to 8 years, self-complete version for 8–12 years), validated in this age group.^18 19^Parental anxiety up to 1 month after discharge, measured by digital questionnaires at discharge, 7 days and 28 days after discharge by the anxiety items on Hospital Anxiety and Depression Scale.^20^Overall paediatric health was measured by digital questionnaires of International Consortium for Health Outcome Measurement (ICHOM) Patient-Reported Outcomes Measurment Information System (PROMIS) set at discharge, 7, 28 and 90 days follow-ups.

#### Economic evaluation

The economic evaluation aims to relate the incremental costs of an SpO2 threshold of 88% (intervention) with an SpO2 threshold of 92% (control) to the incremental health effects. Both cost-effectiveness analysis and a cost–utility analysis will be performed from a societal and healthcare perspective according to Dutch guidelines with a time horizon of 90 days postdischarge.^21^ Discounting is not necessary as the time horizon is less than 12 months. Costs will be measured from a societal perspective using web-based questionnaires based on the iMTA Medical Consumption Questionnaire and iMTA Productivity Cost Questionnaire at discharge and 90 days after discharge.

Cost categories include:

Healthcare costs (primary/secondary/tertiary care, complementary care and home care).Lost productivity costs of the parents (absenteeism from paid and unpaid work).Patient costs (informal care and other care services paid for by the patients themselves).

Valuation follows Dutch cost guidelines,^22^ with absenteeism from paid work using the friction cost approach. Effect measures in the economic evaluation will include:

Length of hospital stay.Overall paediatric health by ICHOM PROMIS set.Parent anxiety.Quality-adjusted life-years (EQ-5D-Y with Dutch reference values).^23^

#### Sample size and feasibility

The sample size calculation is based on the mean time to meet all discharge criteria for the two groups. We aim to demonstrate a difference of 12 hours, determined as a relevant reduction through patient/parent interviews and supported by previous research.^8^ With a mean length of stay of 72 hours and an SD of 48 hours (based on 5 years of admissions data for respiratory distress at our hospital, Statistics Netherlands (Centraal Bureau voor Statistiek (CBS)) data on admission duration and previous research^8 9^) an alpha of 0.05 and 80% power, 251 children are to be included in both intervention and control groups. With an estimated dropout rate of 10%, the goal is to include 560 patients over the 30-month inclusion period. This is feasible, as two participating centres admit an average of 200 children aged 0–12 years with respiratory disease per year. Estimating 80% eligibility, 15% not approached and 60% willingness to participate (based on parent interviews, in-hospital data and expert estimation), and with 10 participating, centres over 30 months up to 2000 children could be included.

#### Patient screening and recruitment

Potential subjects and their parents/caregivers will first be informed using posters at the emergency department. Eligible subjects and their families will be screened by the attending physician and, if eligible, will be asked for informed consent by either their attending physician or an independent study nurse or doctor (see informed consent form, online supplemental file 2).

Conditional informed consent: For patients meeting all inclusion criteria at admission but not (yet) in need of supplemental oxygen, parents/guardians will be asked to sign informed consent conditionally. If the need for supplemental oxygen arises, consent is verbally confirmed and documented in the medical chart. If no supplemental oxygen is indicated during admission, the patient will not be included in follow-up and no additional data will be collected (see figure 1).

**Figure 1 F1:**
[figure not shown]
Informed consent flow chart.

Study initiation: Study procedures begin when at least one parent/guardian provides written informed consent and the second has given verbal consent. Written consent from the second parent/guardian will be obtained within 72 hours after inclusion. The procedure is designed to accommodate emergency situations, where one parent is often present, ensuring the intervention can start as early as possible.

Informed consent process: Adequate time is provided for the informed consent process, allowing parents/guardians to receive information, ask questions, consult with family and consider their decision. For patients already on supplemental oxygen, study enrolment must be completed within 6 hours of the start of oxygen therapy to minimise time spent on supplemental oxygen outside the study protocol. For patients not yet on supplemental oxygen, informed consent is ideally obtained before the need arises but must be completed within 6 hours after the start of oxygen therapy. Beyond this timeframe, children are no longer eligible for participation.

